To achieve our overarching aim, this study will:Establish, in a pragmatic cRCT of the DMMH and other implementation strategies to support its use in service users and clinicians in routine care settings, i) **R**each (i.e., service user participation), ii) **E**ffectiveness (defined as the interaction of efficacy and implementation in real-world settings), operationalized as greater service user engagement at 2-month post-baseline in the experimental than control condition as primary outcome, iii) **A**doption (i.e., proportion of service users and clinicians having used DMMH components in routine care), iv) **I**mplementation (defined as delivery of the DMMH as intended in routine care) and v) **M**aintenance (defined as the extent to which the DMMH becomes sustainable part of routine care at 6-month and 12-month post-baseline). Consistent with the **RE-AIM** framework [16], this will provide the basis for assessing the public health impact of implementation and scale-up of ESM-based monitoring, reporting and feedback via the DMMH and other implementation strategies. The primary hypothesis will be that, compared with the control condition (i.e., Treatment-As-Usual (TAU)), patient-reported service engagement, assessed with the total score of the Service Attachment Questionnaire (SAQ) at 2-month post-baseline (primary outcome), will be higher in the experimental condition (DMMH + additional implementation strategies + TAU), while controlling for service user engagement and clinical unit at baseline (please see our preregistration published on the Open Science Framework (OSF) [15] for further details on all hypotheses).Understand how service users leverage DMMH to support their health and well-being, and evaluate the process of implementing ESM-based monitoring, reporting and feedback in routine clinical care pathways using a realist evaluation framework [17] to identify in vivo configurations of contexts, processes and mechanisms of action, and how these are associated with outcomes of implementation in service users, clinicians, and managers/system administrators.Investigate the economic costs of the DMMH and other implementation strategies, and determine their cost-effectiveness and cost-utility vis à vis TAU.

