### Study population and clusters

Service users and clinicians comprise the study population in the cRCT, process and economic evaluation in the four European countries, which will be recruited from three clinical units (clusters) in each of the eight clinical sites and, thus, a total of 24 units (clusters). Due to differences in mental health care systems across the four European countries, clinical units (clusters) will vary in structure, service type, and size, which will enhance generalizability of findings and allow implementation to be examined under various conditions. Clinical units (as cluster and unit of randomization) will be community mental health teams (Scotland), tracks (Germany (at the Central Institute of Mental Health Mannheim (CIMH)), inpatient, outpatient and community-based services (Germany (at Psychiatric Centre Nordbaden), Belgium, and Slovak Republic). A clinical unit typically will comprise a multidisciplinary team (i.e., psychiatrists, psychologists, nurses, social workers, occupational therapists). In each of the eight clinical sites, 54 service users will be recruited from three clinical units (i.e., 18 service users per unit), and thus a total of 432 service users (*n*=288 in the experimental condition, *n* =144 in the control condition). In addition, around 100 clinicians of these service users from 24 clusters across all sites are estimated to be recruited in a period of 6 months (see Fig. 1). Recruitment and consent procedures as well as eligibility criteria are described in more detail in Supplementary Material 2.

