### Randomization and blinding

A validated and concealed procedure for randomization will be applied independently of the research team using an unbalanced 2:1 ratio for allocating clinical units to the experimental and control condition stratified by the eight clinical sites without contamination (cross-exposure to the experimental condition). An unbalanced allocation ratio of 2:1 will be used to allow for more detailed investigation of implementation aspects and protect against attrition. This will include an option in the concealed randomization procedure to allocate additional clinical units at each of the eight clinical sites if recruitment rates are lower than expected for some clinical units.

After random allocation of clinical units, clinicians in the experimental condition will be informed about allocation status. This will be done through an independent researcher and not the outcome assessors, who will be blind to allocation status for assessments at baseline, 2-month, 6-month and 12-month post-baseline. Further, there will be an independent contact person, who will not be involved in any assessments, for any questions regarding the recruitment and assessment procedure by service users and clinicians. The trial cannot be fully “blind” because clinicians and service users cannot be masked towards the allocation of clinical units to the experimental or control condition. However, outcome assessors will be blinded to allocation status when assessing eligibility, baseline scores and outcomes at baseline, 2-month, 6-month and 12-month post-baseline. Any data specific to the experimental condition (e.g., on clinical feasibility) will be stored in a separate database. Any breaks in masking will be documented in the trial master file and another blinded assessor will be allocated to repeat the assessment and complete the next set of assessments where possible. To maintain the overall quality and legitimacy of the trial, code breaks will only be done in exceptional circumstances when knowledge of the treatment allocation is absolutely essential for further management of the service user.

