
### Statistical analysis

Statistical analysis will be performed according to the intention-to-treat principle based on a pre-registration and statistical analysis plan (SAP) published on the OSF [15]. Please see the published SAP [15] for further details on the statistical analysis. The primary hypothesis of the effect of condition (i.e., DMMH + additional implementation strategies + TAU vs. TAU) on service engagement as primary outcome (measured with the patient-rated SAQ total score as the dependent variable) will be tested using a fixed effects regression model controlling for unit effects, with a dummy variable for the condition (DMMH + additional implementation strategies + TAU vs. TAU), the SAQ engagement total score at baseline, and a dummy variable coding for the random allocation to ESM outcome data collection. The focal coefficient of the model is the coefficient for the dummy variable for condition, tested via t-test for the null hypothesis of no difference between the two conditions against the two-sided alternative hypothesis that there is a difference at 2-month post-baseline. The experimental condition will be interpreted as having a statistically significant effect in the hypothesised direction if the estimated coefficient indicates a higher SAQ score (i.e., more service engagement) for this condition and the associated t-test is significant at α < .05. The primary endpoint analysis will be based on observed data using Full Information Maximum Likelihood estimation for the linear regression model. As there is minimal missing data expected in baseline and structural variables in the statistical model for the primary endpoint, we will evaluate whether more robust approaches in sensitivity analyses will be needed and would report results based on multiple imputations (please see the SAP [15] for further details).

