We will test the secondary hypotheses of the effect of condition (DMMH + additional implementation strategies + TAU vs. TAU) on personal recovery, self-management, shared-decision making, personal therapy goal attainment, social functioning, social participation, quality of life, and symptom improvement/severity as secondary outcomes using a mixed model (restricted maximum likelihood estimation). First, we will use α < 0.05 to indicate statistical significance, i.e., evidence against the null hypothesis of no difference between the two conditions across all three time points (an average difference between conditions across 2-month, 6-month and 12-month post-baseline) against the two-sided alternative hypothesis that there is a difference; second, we will use, for each secondary outcome, linear contrasts at each of the three follow-up time points to investigate whether there is a potential difference between the conditions (adjusted nominal level α/3 each). The covariates included in the model in addition to the condition indicator will be the respective secondary outcome score at baseline, time (as a three-level factor), the baseline × time interaction, the condition × time interaction, and a dummy variable coding for the random allocation to ESM data collection at baseline. In addition to p-values, 95% confidence intervals for the time-specific treatment effects will be calculated. Clustering of measures within clinical units (and of repeated measures within participants) will be taken into account by allowing residuals within clinical units (and participants) to be correlated with an unstructured variance-covariance matrix. As ESM data have a multilevel structure, multiple ESM observations (level 1) will be treated as nested within time points (i.e., 2-month, 6-month, and 12-month post-baseline) (level 2) and time points will be treated as nested within participants (level 3). Additional analyses will investigate between-site effects (via condition-site interactions) and associations with unit-level characteristics. Another set of additional analyses will investigate a potential ESM method effect on primary and secondary outcomes due to ESM outcome data collection alone (based on the within-trial randomisation of participation in ESM outcome data collection).

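### The secondary mixed models omit site, the randomisation stratum, so the standard error of the condition effect is too large if sites still differ after baseline adjustment

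*Protocol article*

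**What the plan says.** Design. The Randomization and blinding section allocates clinical units 2:1, "stratified by the eight clinical sites without contamination". Under Study population and clusters, participants are "recruited from three clinical units (clusters) in each of the eight clinical sites". With 24 units split 16 to 8, this implies two experimental units and one control unit at each site.

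Secondary models. The Statistical analysis section states: "The covariates included in the model in addition to the condition indicator will be the respective secondary outcome score at baseline". The rest of the list is time as a three-level factor, baseline by time, condition by time, and the dummy for allocation to ESM data collection. Clustering is handled by "allowing residuals within clinical units (and participants) to be correlated with an unstructured variance-covariance matrix". Site is in neither place. It comes up afterwards, outside the hypothesis tests: "Additional analyses will investigate between-site effects (via condition-site interactions".

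Primary model. The same section specifies a "fixed effects regression model controlling for unit effects, with a dummy variable for the condition", together with "the SAQ engagement total score at baseline, and a dummy variable coding for the random allocation to ESM outcome data collection". The primary hypothesis in the Background is worded in the same way: "while controlling for service user engagement and clinical unit at baseline".

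**The concern.** When allocation is balanced within sites, a difference shared by all units of a site cancels out of the comparison of conditions. The analysis gets the benefit only if the model knows about sites. A model with correlation at unit level alone treats what units of one site share as independent unit-to-unit variation, and charges it to the standard error of condition.

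Site differences are plausible here. The sites lie in four countries with different health-care systems, and the article expects units to differ in structure, service type and size. What is at stake is precision: wider confidence intervals than the design warrants and lower power for the secondary outcomes.

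**Working it through.** **Inputs.** From the article: 8 sites, 3 units per site, 16 experimental and 8 control units, ICC 0.05, d = 0.4, two-sided α = 0.05. The number analysed per unit follows from the Sample size calculation, taking its 201 as given: 201 × (1 + 7.38 × 0.05) = 201 × 1.369 = 275.2; 275.2/24 = 11.5, rounded up to 12 per unit, so 288. This step reproduces the article's figure. Assumed, because the article does not give it: the share of the ICC that lies between sites.

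**Formulae.** Take total variance 1 and one follow-up time point. Let s be the site variance, u the unit-within-site variance (s + u = 0.05) and 0.95 the residual variance.

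- Variance of a unit mean within its site: v = u + 0.95/12 = u + 0.0792.
- True SE of the condition difference (site cancels): √[v × (1/16 + 1/8)].
- Mean square that a model without site expects, pooled within conditions on 22 df. The 16 experimental units contribute 16 × (7/8) × s = 14s, since they share sites in pairs; the 8 control units contribute 7s. So MS = (22v + 21s)/22 = v + (21/22)s.
- SE reported without site: √[MS × (1/16 + 1/8)].

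**Worked line, site share 50%.** s = u = 0.025. v = 0.1042; true SE = √(0.1042 × 0.1875) = 0.1398. MS = 0.1042 + 0.0239 = 0.1280; reported SE = √(0.1280 × 0.1875) = 0.1549. Ratio = 1.109.

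**All shares.** Type I error and power are from 20,000 simulated sets of 24 unit means per scenario, analysed without site (22 df) and with site as a fixed effect (15 df).

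| Site share of ICC | True SE | SE without site | Ratio | Type I error without / with site | Power at d = 0.4 without / with site |
|---|---|---|---|---|---|
| 0% | 0.1556 | 0.1556 | 1.000 | 0.053 / 0.052 | 0.693 / 0.675 |
| 25% | 0.1479 | 0.1553 | 1.050 | 0.042 / 0.049 | 0.701 / 0.718 |
| 50% | 0.1398 | 0.1549 | 1.109 | 0.032 / 0.051 | 0.713 / 0.762 |
| 75% | 0.1311 | 0.1546 | 1.179 | 0.024 / 0.050 | 0.725 / 0.815 |

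At a total ICC of 0.10 the ratios are 1.000, 1.077, 1.176 and 1.310. The power column borrows the primary endpoint's effect size, because the article states none for the secondary outcomes; read it as a guide to the difference between the two analyses.

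**Allowing for the baseline score.** The table applies if 0.05 is the ICC after baseline adjustment. If 0.05 is the raw ICC, site and unit differences are stable over time, and the individual baseline–follow-up correlation is 0.5 (all assumptions), then adjustment with slope 0.5 leaves (1 − 0.5)² = 25% of the site and unit variances and 1 − 0.5² = 75% of the residual. At a 50% share: s = u = 0.00625, residual 0.7125. v = 0.00625 + 0.7125/12 = 0.0656; MS = 0.0656 + (21/22) × 0.00625 = 0.0716; ratio = √(0.0716/0.0656) = 1.045. With t critical values of 2.131 (15 df) and 2.074 (22 df), the interval with site is (2.131/2.074)/1.045 = 0.98 times as wide, about 2% narrower.

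**Primary model.** The 24 unit indicators have rank 24. Adding the eight site indicators leaves it at 24, so site is already contained. Adding condition also leaves it at 24, so condition cannot be separated from the units. Site and condition together, without unit indicators, have rank 9 (8 + 1), so a site-adjusted condition effect can be estimated.

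**The case against.** Four points can be made on the other side.

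- The gain depends on a quantity that the article does not report. If sites do not differ after adjustment, adding site costs a little power (0.693 to 0.675). This stands, and is why the size is given as a range.
- The baseline score of the same outcome is in the models and removes part of any stable site difference. This also stands: it brings 11% down to about 4–5% in the illustration.
- The fault is conservative. It neither biases the estimate nor raises the false-positive rate. Correct, and it limits the seriousness.
- Site is examined in additional analyses, and the published SAP, which is not at hand, may include it in the main models. The interaction analyses do not repair the standard error of the main test. The SAP may do so, but the article sets out a covariate list that reads as complete and leaves the stratum out, so the two would then need to be reconciled.

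A reader might also infer that the primary analysis has the same fault. The text does not support that. Fixed unit effects contain the site effects because each unit belongs to one site, so no between-site variance can reach the standard error. The difficulty in that model is a different one: condition is constant within units and is absorbed as well. Nor can the omission be asserted for the ESM outcome models, for which the article describes the nesting but gives no separate covariate list.

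**Conclusion.** The point holds for the secondary mixed models. Followed as written, they leave between-site variance in the standard error of condition although the randomisation has balanced it out. The inflation is 0 to 18% for site shares of 0 to 75%, assuming a total ICC of 0.05 after adjustment, 12 analysed per unit, two experimental units and one control unit at every site, and a single time point in place of the three-time-point model. It is smaller where the baseline score absorbs stable site differences, and also where fewer than 12 per unit are analysed, since the residual term then weighs more.

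The larger gains, such as power rising from 0.725 to 0.815, belong to a 75% site share that nothing in the article establishes. For the primary model the point is conditional: it arises only when the fixed unit effects are replaced by random unit effects or cluster-robust errors. This is a loss of precision worth correcting and no threat to the validity of a positive result.

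**What to change.** Add site, as the eight-level randomisation stratum, as a fixed effect in the secondary mixed models, with clinical unit random within site, and amend the covariate list in the Statistical analysis section to say so. If the SAP already includes site, bring the two texts into line; if site is left out on purpose, give the reason.

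When the primary model is restated in an estimable form (random unit effects or cluster-robust errors), include site as a fixed effect there too.

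No new data are needed, since site is known for every unit. The cost is 7 cluster-level degrees of freedom (22 to 15), which is about 1 to 2 points of power if sites do not differ.

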### Economic evaluation

The economic evaluation serves the dual objective of providing information on the costs and cost structure of delivering the DMMH and other implementation strategies under different health care systems and of establishing the intervention’s value for money. As such, it will include both a micro-costing study, cost-effectiveness and cost-utility analysis conducted based on data collected as part of the cRCT. Specifically, we will adopt an activity-based approach to costing and estimate the economic costs of all key intervention activities including administration of DMMH by clinicians and delivery of implementation strategies during the implementation phase. We will use the EQ-5D-5L [29] to assess quality-adjusted life years (QALYs) and the CSRI [24] to assess use of health services, social care, informal care, and production losses as a basis for the economic evaluation. The cost-effectiveness analysis will combine cost data with patient-reported service engagement using the SAQ total score at 2-month post-baseline as the primary outcome of the cRCT. Incremental cost-effectiveness ratios (ICER) will be calculated as a measure of the incremental cost incurred by the DMMH and implementation strategies relative to their incremental benefits (based on the SAQ total score at 2-month post-baseline) in the experimental vs. control condition. Cost-utility analysis will combine cost data with quality-adjusted life years (QALYs) derived from the EQ-5D-5L and relate the incremental cost incurred by the DMMH and implementation strategies to QALYs gained at 2-month, 6-month and 12-month post-baseline in the experimental vs. control condition. In addition, we will investigate the potential cost savings which is likely generated by the expected reduction in the use of care services monitored by the CSRI [24].

### Regulatory requirements and research governance

Regulatory requirements by EU MDR 2017/745, relevant DIN EN ISO norms and IEC standards need to be addressed and overcome for successful implementation of ESM-based monitoring, reporting and feedback via the DMMH in mental health care practice. The current study is carried out as an ‘Other Clinical Investigation’ according to §82 of the EU MDR 2017/745 and its national implementation in Belgium, Germany, and Slovak Republic, relevant national legislation in Scotland and the UK, EN DIN ISO 14155 and associated DIN EN ISO norms and IEC standards. CIMH is the sponsor of this ‘Other Clinical Investigation’, which forms part of Work Package 7 (WP7) “Implementation Strategies, Processes, Outcomes and Costs” of the EU IMMERSE consortium, with the sponsor of this EU consortium being KU Leuven. The ‘Other Clinical Investigation’ has received ethics approval by IECs and, where required by national legislation, formal notification of (i.e., BfArM (Germany), or approval by (i.e., FAGG (Belgium), ŠUKL (Slovak Republic)), relevant regulatory authorities was obtained (Belgium, EUDAMED No. CIV-22-08-040547-SM01; Germany, DMIDS No. DE-22-00013961; Scotland, Ref. No. 22-WS-0125; Slovak Republic, EUDAMED No. CIV-SK-22-08-040547). Amendments to the study protocol will be submitted to the relevant IEC and regulatory authorities, then communicated to all relevant parties (DMEC, TSC, the sponsor of the clinical investigation (CIMH), funder, and collaborating centres) and will be updated in the clinical trial registry. The trial has been prospectively registered with the ISRCTN registry (ISRCTN15109760, registration date: 03/08/2022). Deviations from the study protocol are monitored across all sites and managed centrally by the sponsor of the clinical investigation (CIMH). The handling of the data will be in compliance with the European General Data Protection Regulation (GDPR) and relevant DIN EN ISO norms and IEC standards. The Therapy Designer and movisensXS (for ESM outcome data collection) platforms are hosted by movisens GmbH. The research database, analysis and compute area are hosted by the data management team at Friedrich-Alexander-University Erlangen-Nuremberg. All outcome data collected will be checked for quality on an ongoing basis, archived and integrated for analysis by the data management team. Access to the locked trial data set will be provided by the data management team to the trial statistician and investigators only after completion of data collection, checking/cleaning as well as publication of the SAP on the OSF. Further details on research governance are reported in Supplementary Material 6.

## Discussion

While the mental health field has seen a growing interest in the use of digital tools for person-centred care, uptake in routine practice remains limited. The IMMERSE effectiveness-implementation study sets out to address this challenge and, in doing so, contains several novel and unique aspects. To our knowledge, the DMMH is the first ESM-based monitoring device that has been developed and is evaluated and implemented in line with the EU MDR 2017/745 and associated DIN EN ISO norms and IEC standards. It will, thus, allow for ESM-based monitoring (via the MoMent App), reporting and feedback (via the MoMent Dashboard) in routine mental health care. As such, it reflects a step change in regulatory-compliant delivery of digital interventions and services in the mental health field and will be key in facilitating more rapid ecological translation of digital innovations to routine care [2, 30]. Further, the DMMH was developed in line with principles of human-centred design research for delivery as a technology-enabled service [12], facilitated by a firm set of technological, user- and stakeholder-centred implementation strategies. The pragmatic effectiveness-implementation trial design combined with a process and economic evaluation, which is implemented across eight sites in four European countries in line with relevant CONSORT guidelines, research governance procedures required by all academic and clinical partners, as well as national medical device legislation and regulation, will allow to endorse the methodological rigour of a cRCT, whilst providing high external validity of findings on reach, effectiveness, adoption, implementation, and maintenance. Coupled with the work carried out in the wider EU IMMERSE consortium, which aims to elucidate the diverse ethical, legal and policy challenges and practical requirements for clinical implementation of digital innovations in routine mental health care, this study will contribute to the digital transformation of mental health care in Europe and advance true person-centred care, empowering service users as active partners in their treatment, self-management, and decision-making.

